| Demographics                                                        |                                  | X                                                         |                                                   |                           |                           |                                                         |                                               |
| Medical and illness history                                         |                                  | X                                                         |                                                   |                           |                           |                                                         |                                               |
| Collect vital signs
(HR, RR, temperature)                 |                                  | X                                                         |                                                   |                           |                           |                                                         |                                               |
| Weight (obtained from clinical chart)                        |                                  | X                                                         |                                                   |                           |                           |                                                         |                                               |
| Review of systems                                                   |                                  | X                                                         |                                                   |                           |                           |                                                         |                                               |
| Concomitant medication review                                       |                                  | X                                                         |                                                   |                           |                           | X                                                       |                                               |

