## 2.3 RISK/BENEFIT ASSESSMENT

### 2.3.1 KNOWN POTENTIAL RISKS

The overall risk associated with oral ondansetron administration is exceedingly low. In a post-marketing analysis and systematic review of the published literature, grey literature, manufacturer's database, Food and Drug Administration Adverse Events Reporting System, and the World Health Organization Individual Safety Case Reports Database (VigiBase); no documented (or perceived) arrhythmias were identified within 24 hours of single oral dose ondansetron administration. Sixty unique reports were identified describing an arrhythmia associated with ondansetron administration (any dose, frequency). A significant medical history (67%) or concomitant use of a QT-prolonging medication (67%) was identified in 83% of reports. Approximately one third occurred in patients receiving chemotherapeutic agents, many of which are known to prolong the QT interval. An additional third involved administration to prevent post-operative vomiting.

In a retrospective study the risk of ventricular arrhythmia within 24 hours after ondansetron administration was 3 in every 100,000 patients treated annually (0.003%). All 7 patients in whom an arrhythmia occurred had underlying congenital cardiac conduction abnormalities ( $n = 3$ ) or other major cardiac diagnoses ( $n = 4$ ). The authors concluded that the findings do not support electrocardiogram screening or continuous monitoring of other pediatric populations receiving ondansetron.

Ondansetron is a 5-HT3 receptor antagonist indicated for the prevention of:

- nausea and vomiting associated with highly emetogenic cancer chemotherapy
- nausea and vomiting associated with initial and repeat courses of moderately emetogenic cancer chemotherapy
- nausea and vomiting associated with radiotherapy in patients receiving either total body irradiation, single high-dose fraction to the abdomen, or daily fractions to the abdomen
- postoperative nausea and/or vomiting

Contraindications include:

- known hypersensitivity (e.g., anaphylaxis) to ondansetron or any components of its formulation
- concomitant use of apomorphine (a non-opioid medication indicated for the treatment of vomiting or Parkinson's disease)

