#### Warnings and Precautions:

- QT interval prolongation and Torsades de Pointes: Avoid in patients with congenital long QT syndrome; monitor with electrocardiograms (ECGs) if concomitant electrolyte abnormalities, cardiac failure or arrhythmias, or use of other QT prolonging drugs;
- Serotonin syndrome: Reported with 5-HT3 receptor antagonists alone but particularly with concomitant use of serotonergic drugs;
- Masking of progressive ileus and/or gastric distention following abdominal surgery or chemotherapy-induced nausea and vomiting

Adverse reactions most frequently reported are headache, constipation, feeling of warmth, and flushing. There have been rare reports of tachycardia, angina (chest pain), bradycardia, hypotension, syncope, electrocardiographic alterations, seizures, rash, and hypersensitivity reactions.

Taking in to account our carefully chosen inclusion and exclusion criteria, the risk of adverse events is low in the population of children who will be enrolled in this study. Given the broad use of ondansetron, and the potential benefit associated with the outpatient use of this medication following ED discharge, it is vital that we determine if any benefit is accrued related to its use.

---

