### 2.3.3 ASSESSMENT OF POTENTIAL RISKS AND BENEFITS

The main risks associated with this protocol are associated with the administration of oral ondansetron. Study questionnaires are designed to minimize questions which may be perceived as intrusive. To minimize risk associated with the administration of multi-dose ondansetron, the study inclusion and exclusion criteria were carefully selected to avoid known contraindications. Patients who have a known hypersensitivity or allergy to ondansetron or other serotonin receptor antagonist, a history of prolonged QT syndrome or presence of heart disease or arrhythmia, as well as individuals taking SSRI, SNRI, apomorphine, macrolide antibiotics or any medication accepted as causing torsades de pointes will be excluded from participation in the study.

Study medication will be administered at home by the participants' caregiver on an 'as needed' basis. Doses will be based on the weight of the participant at time of enrollment. Trained study research staff will calculate the appropriate dose of study medication to be administered. The dose information will be recorded on discharge instructions provided to the caregiver and the volume of study medication will be marked on a syringe to minimize measuring errors. Research staff will provide one-on-one teaching and printed instructions on how to administer the doses to the participant prior to participant discharge from the ED to minimize the risk of incorrect dosing.

Participants will be contacted 24, 48, and 168 hours (7 days) after randomization to obtain outcome endpoint data and determine if there have been any adverse events (e.g. diarrhea, constipation, headache, etc.). Data regarding ongoing vomiting, diarrhea, and/or fever, and return to healthcare will be collected during scheduled follow-up calls/emails. Caregivers can also provide general information regarding the child's illness or any other symptoms the child may be experiencing when completing the scheduled follow-up questionnaires. This information will be reviewed by a trained research team member for any possible adverse events or symptoms that may require medical care.

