### 5.2 EXCLUSION CRITERIA

Research staff will ensure selection of participants is fair and equitable in accordance with Article 4.1 of the Tri Council Policy Statement: *"Researchers shall not exclude individuals from the opportunity to participate in research on the basis of attributes such as culture, language, religion, race, disability, sexual orientation, ethnicity, linguistic proficiency, gender or age, unless there is a valid reason for the exclusion"*

In this study, language barrier may be listed as an exclusion criteria due to the amount of communication needed for the follow-up portion of the study and the potential risks associated with administration of ondansetron. If the participant is unable to speak English or French, and the study team is unable to find an individual who speaks the participant's language (family member, hospital translator, etc.), they will not be consented or enrolled in the study. Similarly, because communication is a key piece of the study, if a person is unable to provide follow-up and comprehend the informed consent form they will not be able to participate in the study.

Individuals who meet **any** of the following criteria will be excluded from participation in this study:

1. Bilious (having a green or bright yellow colour, indicating larger amounts of bile in the stomach) or bloody vomit during current illness: *This may indicate an alternate diagnosis.*
2. Known hypersensitivity to ondansetron or any serotonin receptor antagonist (e.g. palonosetron, dolasetron, granisetron).
3. Known allergic reaction to components of ondansetron (*citric acid, sodium benzoate, sodium citrate dihydrate, and strawberry flavor, sorbitol*) or the placebo medication (*methylparaben, glycerin, citric acid, potassium sorbate, sorbitol, strawberry flavor*)
4. History or family history (first degree relative) of prolonged QT syndrome
5. Presence of complex congenital heart disease
6. History or family history (first degree relative) of cardiac arrhythmia
7. Concomitant use of (within the past 48 hours OR being prescribed) any of the following – *For a full list of possible medications in the following categories, please references the TMOP:*
  - a) QTc prolonging medications (e.g. methadone, anti-depressants, antiarrhythmics)

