### 5.5 STRATEGIES FOR RECRUITMENT AND RETENTION

Participants will be recruited from six EDs across Canada. Patients will be approached for permission to participate in research according to local policy and procedure. Only patients who have been administered a minimum of 1 (one) dose of ondansetron by the clinical team will be approached for participation in the study.

To ensure study retention, trained research study staff will review the study in detail with the patient and/or caregiver emphasizing the risk, benefits, and time commitment required prior to consent.

Follow up will be performed 24 and 48 hours following enrollment, as well as on Day 7 (168 hours after enrollment). Caregivers will have the opportunity to complete follow-up by email or telephone. If no response is received via email within 24 hours of the email send time, a follow-up telephone call will be performed to obtain the necessary data. If unable to make contact via telephone within the first 24 hours, 3 (three) additional attempts per follow-up time point will be made to contact the caregiver and/or participant by telephone over the subsequent 5-14 days.

There will be no financial reimbursement associated with this trial.

*For a more detailed description of recruitment and retention plans, see the TMOP and site specific SOPs.*

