#### 6.4 STUDY INTERVENTION COMPLIANCE

After randomization and treatment assignment, the qualified research team member will complete a study medication dispensation form which contains the blinded kit number, expiration date, participant study ID, participant weight and age at time of enrollment, dose dispensed, the name and signature of the dispensing staff member, and the date and time of dispensation.

A drug accountability log will also be maintained at all participating institutions containing the initials of the qualified research team member dispensing the intervention to the participant caregiver, the kit number used, the accompanying participant study ID and date and time of dispensation.

The qualified research team member will demonstrate to the caregiver how to measure and dose the study medication. The exact volume in milliliters of the 4mg/5mL solution will be calculated by the research team member using REDCap prior to the caregiver leaving the ED.

The caregiver will be instructed to provide one dose every 8 hours to a maximum of 3 doses in a 24 hour period for 48 hours after discharge from the ED, as they feel their child requires the intervention. **The caregiver may choose to administer a minimum of zero to a maximum of six doses (excluding vomited doses) to the participant. If the caregiver does not administer any doses of the study intervention; the participant is still considered compliant with the study protocol.**

The number of doses administered to the participant by the caregiver will be recorded via telephone or email questionnaire performed 24 and 48 hours after enrollment (*Time 0 – Consent Date and Time*). Caregivers will be asked to return unused study medication and/or empty bottles to the study team or to a community pharmacy for destruction after the completion of the 7 day follow up period.

The participant will be considered not compliant with the protocol if the study team is unable to contact the caregiver/participant for the follow-up schedule as detailed in the SoA (section 1.3) to a maximum of 21 days after enrollment.

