## 8 STUDY ASSESSMENTS AND PROCEDURES

### 8.1 EFFICACY ASSESSMENTS

Primary and secondary endpoints will be determined by the outcome measures. Assessments performed will support the outcome measures listed in Section 3.0 Objectives and Endpoints.

**Screening:** Participants presenting to the ED of a participating institution will be screened for eligibility using the eligibility criteria listed in sections 5.1 and 5.2 by a trained research team member. The research team member will ask the caregiver questions related to the patient's medical history and current medications that may be contraindicated. Inclusion/exclusion criteria will be determined based on caregiver report of patient's medical history and the details of their current illness. This information will be confirmed with the treating physician to ensure accuracy of reported information and medical oversight. In addition to the patient's medical history, eligibility depends on the treating physician ordering at least 1 dose of ondansetron while the patient is still in the ED, as well as the patient's ED diagnosis. This information will be confirmed using physician or nursing orders and the patient's ED medical chart by the research team member. Permission to access the patient's chart for screening purposes will be obtained from the caregiver/legally authorized individual, in accordance with provincial access to health information legislation.

**Enrollment/Baseline Assessments (outcome assessment):** A baseline questionnaire will be performed to obtain information supporting the study's outcome measures (e.g. *current medical history, duration and frequency of vomiting, presence of fever, duration and frequency of diarrhea, satisfaction scale, etc.*).

In addition to the questionnaire listed above, the trained research team member will obtain the participant's heart rate (HR) and respiratory rate (RR) at the Enrollment/Baseline visit. The triage temperature and weight will be obtained from the ED medical record. To obtain a baseline understanding of the participant's health and medical condition, a basic review of systems and concomitant medications will also be performed.

**Follow-up:** Outcome measure end-point data will be obtained using follow-up questionnaires performed 24, 48, and 168 hours (7 days) after the Baseline/Enrollment visit Time 0 (Consent date and time) by research study staff. Questions will be asked related to the following:

- Frequency and duration of vomiting

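### Section 2.3.3 says heart disease is excluded, but criterion 5 in 5.2 names only complex congenital heart disease, so a child with cardiac failure can be eligible with no scheduled ECG

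*Combined protocol and SAP*

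**What the plan says.** Section 2.3.3 presents the eligibility criteria as the means of limiting risk. Among the patients to be excluded it lists those with "a history of prolonged QT syndrome or presence of heart disease or arrhythmia", and it does not qualify 'heart disease'.

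Section 5.2 is narrower. Criterion 5 reads "Presence of complex congenital heart disease". Criteria 4 and 6 exclude a personal or first-degree family history of prolonged QT syndrome and of cardiac arrhythmia. Criterion 7 excludes by drug, including QTc-prolonging drugs (antiarrhythmics are an example) and drugs that disturb electrolytes (diuretics are an example). It refers to the TMOP for the full list. No criterion in 5.1 or 5.2 names cardiac failure.

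Section 8.1 settles which text governs enrolment: patients "will be screened for eligibility using the eligibility criteria listed in sections 5.1 and 5.2".

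On the hazard, the Warnings and Precautions in Section 2.3.1 say to "monitor with electrocardiograms (ECGs) if concomitant electrolyte abnormalities, cardiac failure or arrhythmias, or use of other QT prolonging drugs". The vital signs in the Section 1.3 schedule are "HR, RR, temperature", and no ECG appears among the procedures. Under Section 6.4 a caregiver may give "a minimum of zero to a maximum of six doses" at home.

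**The concern.** The protocol gives two accounts of who is kept out on cardiac grounds, and the account that sites apply is the narrower. Someone who judges the risk from Section 2.3.3, such as an REB or data and safety monitoring board member, would believe that no child with heart disease is enrolled. A site that follows Section 5.2 to the letter could enrol a child with cardiac failure.

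This matters because the protocol itself names cardiac failure as a state that calls for ECG monitoring. The same precaution names arrhythmia, which has its own exclusion (criterion 6). Cardiac failure has neither an exclusion nor a scheduled ECG. At stake is the safety of a small number of children and the accuracy of the risk statement. The treatment comparison is not at stake.

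**Working it through.** The plan states no figure on this point, so the main check is a comparison of texts.

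**Step 1. Put a test case through Section 5.** Take a child with cardiac failure who has no personal or first-degree history of prolonged QT or arrhythmia, takes no criterion 7 drug, and otherwise qualifies.

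| Provision | Does it exclude this child? |
|---|---|
| 5.1, all inclusion criteria | No; none concerns cardiac status |
| 5.2 criterion 4 (prolonged QT, own or family) | No |
| 5.2 criterion 5 (complex congenital heart disease) | No |
| 5.2 criterion 6 (arrhythmia, own or family) | No |
| 5.2 criterion 7 (drugs) | No, by construction |
| 6.5 (concomitant therapy) | No; it repeats drug exclusions only |
| 2.3.3 (narrative) | Says yes, but it is not the list used for screening |

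The child is eligible under Section 5 and described as excluded in Section 2.3.3.

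**Step 2. Look for a check elsewhere that would stop enrolment.**
- Section 8.2, screening: the history is reviewed in relation to the eligibility criteria and confirmed by the treating physician. A diagnosis missing from the criteria need not be asked about.
- Section 8.2, review of systems: it covers the cardiovascular system and precedes the first study dose, but it follows the finding of eligibility.
- Sections 7.1 and 7.2: the investigator may change management or withdraw a participant. Both are discretionary.
- Section 1.3: no ECG.

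None of these is a written exclusion.

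**Step 3. Give the scale of the background risk.** Section 2.3.1 reports 3 ventricular arrhythmias per 100,000 patients treated annually, within 24 hours of ondansetron. With 1:1 allocation of 1030 children:

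- active arm = 1030 / 2 = 515
- expected events at that rate = 515 × 3 / 100,000 = 0.015

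This is a whole-population rate. Section 2.3.1 gives neither the route nor the number of doses behind it. The rate in children with major heart disease would be higher, but no denominator is given for them.

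**Step 4. See what the case series can show.** Of the 7 arrhythmia cases, 3 (3/7 = 43%) had congenital conduction abnormalities and 4 (4/7 = 57%) are described by the phrase "or other major cardiac diagnoses". The text does not say what those four diagnoses were. Some or all could have been complex congenital disease (criterion 5) or could have come with an arrhythmia history (criterion 6). The number falling in the gap is anywhere from 0 to 4 of 7.

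**The case against.** The strongest case against the point is that the gap is already almost closed.

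- Many children with cardiac failure would be caught by an arrhythmia history, an antiarrhythmic or a diuretic.
- Every child has already had ondansetron from a clinician: "Only patients who have been administered a minimum of 1 (one) dose of ondansetron by the clinical team will be approached" (Section 5.5).
- The treating physician confirms the history, a cardiovascular review precedes the first study dose, and Section 7.2 allows withdrawal for a medical condition.
- The primary objective speaks of previously healthy children.
- The schedule does not forbid an ECG on clinical grounds.
- Section 2.3.1 lists cardiac failure as a precaution and has no cardiac item among the contraindications. It also cites a review that found no arrhythmia within 24 hours of a single oral dose.

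Most of this stands as a limit on size: the number affected is probably very small. It does not remove the contradiction. Previously healthy is a phrase in the objective and not a criterion. The clinician's choice concerned ED dosing, not up to six blinded doses at home. The reassuring review concerns single doses. The other checks rest on judgement or on drug use, not on the diagnosis.

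It is also fair that Section 2.3.3 is a short summary and may simply be the looser text. If so, that section is wrong and still needs correcting.

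A reader might infer that 57% of known arrhythmia cases lie in this gap. The documents do not support that, because the four diagnoses are not described. A reader might also stretch the gap to cardiomyopathy or acquired heart disease as named groups, or want every minor lesion excluded. The first two terms appear nowhere in the protocol, and nothing in it identifies minor lesions as a risk. The condition that the protocol names is cardiac failure.

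**Conclusion.** The point holds as a minor safety and consistency matter. Sections 2.3.3 and 5.2 disagree in the current text, and the text that governs enrolment leaves a child with cardiac failure eligible in the circumstances set out above, with no scheduled ECG.

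The number of such children cannot be estimated from the documents: they give no prevalence, and the full criterion 7 drug list is in the TMOP. The 0.015 expected events describes all treated children and is not an estimate for this subgroup. Nor is there evidence here of appreciable arrhythmia risk in the trial as a whole. Sample size, power and the primary analysis do not change.

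The conclusion assumes that sites apply Section 5.2 as written, as Section 8.1 says, and that the TMOP adds no cardiac exclusion of its own.

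**What to change.** Extend criterion 5 so that, after complex congenital heart disease, it continues: *cardiac failure or other major cardiac diagnosis*. Put the same wording in Section 2.3.3 in place of the unqualified heart disease. The first added term comes from the precaution in Section 2.3.1 and the second from that section's description of the arrhythmia cases, so the change stays within the protocol's own evidence and leaves minor lesions eligible. Because *other major* invites judgement, a short list of examples in the TMOP would keep sites consistent.

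Narrowing Section 2.3.3 to match 5.2 would also remove the contradiction. It would leave cardiac failure eligible without an ECG, however, and would need a justification against the precaution.

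The cost is one line in criterion 5 and one phrase in 2.3.3, REB approval of the amendment, a briefing at the six sites, and a few more screen failures. The target of 1030 and the analysis stay as they are.
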